### Setting

The trial setting is the city of Toronto with a population of at 2.5 million served by an emergency medical services system employing approximately 430 Advanced Life Support Paramedics, 570 Basic Life Support Paramedics and 3,000 Firefighter first responders under the same medical direction. In addition, the trial includes one Ornge Transport Medicine rotor wing base with two helicopters and 32 critical care flight paramedics providing responses from accident scenes outside the city of Toronto within south central Ontario. Enrolled patients will be directly admitted to two adult designated regional Trauma Centers.

### Intervention Protocol

All patients will be treated according to research medical directives (Additional File 2) based on a standardized provincial out of hospital trauma treatment protocol [6]. The study solution is started within 4 hours of the time the emergency call was received at ambulance dispatch. Samples of peripheral blood will be collected upon emergency department (ED) arrival, 12, 24 and 48 hours after ED arrival from a vein remote from the venous access site for the study infusion. Blood samples will be collected in heparinized and non-additive vacutainers by a single trained lab technician and immediately (within 1-h) shipped to a single designated laboratory for whole blood flow cytometric cellular analyses and measurement of circulating molecular immuno-inflammatory markers. Serum will be frozen for subsequent analyses. Whole blood will be incubated with saturating concentrations of the adhesion (CD62L-FITC, CD11b-PE), degranulation (CD66b-FITC, CD63-PE), apoptotic/necrotic (Annexin V-PE, 7-AAD, Active Caspase-3, CD95-Fas, CD178-FasL) markers, in conjunction with CD14-APC surface staining (to differentiate leukocyte subsets). Results will be acquired on a Becton Dickinson dual-laser (488 nm and 635 nm) BD FACSCalibur flow cytometer using CellQuest software. Serum samples will be analyzed for pro-/anti-inflammatory cytokines (TNF-α, IL-10), soluble leukocyte and endothelial-derived adhesion molecules (sICAM-1, sVCAM-1, sE-selectin, sL-selectin), pro-/anti-apoptotic molecules (sCD95, sCD95L, TNF-RI, sFas/FasL) and neuro-biomarkers of brain injury (S100B, NSE, MBP) (Additional File 3).

Magnetic Resonance Imaging on a 1.5 Tesla General Electric Signa Magnet is planned for completion at 4 months for consenting patients using a standardized protocol (Additional File 4, 5, 6, 7); a 3D 1.3 mm thick, T1-weighted, series (TE 4-2, TR 35, flip angle 35), an interleaved 3 mm thick PD and T2-weighted spin echo sequence (TE 39/80, TR 3000, flip angle 90) (Additional File 6), a gradient echo sequence and Diffusion Tensor Imaging (11 directions) (Additional File 7); tissue segmentation and parcellation including lesion quantification [7-12] using previously published in-house software as well as ANALYZE software [7,13].

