### Study Objective

The primary objective of this study is to report feasibility in accordance with the methodology described by Lancaster and Dodds [5], specifically addressing:

1) baseline survival rates for the treatment and control group to aid in the design of a definitive multicentre trial;

2) randomization compliance rate;

3) ease of protocol implementation in the out-of-hospital setting;

4) adverse event rate of HSD infusion.

The secondary objectives include measuring the effect of HSD in modulating the immuno-inflammatory response to severe head injury and its effect on modulating the release of neuro-biomarkers into serum; evaluating the role of serum neuro-biomarkers in predicting patient outcome and clinical response to HSD intervention; and evaluating effects of HSD on brain atrophy post-injury and neurocognitive and neuropsychological outcomes.

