### Cellular and Molecular Biomarkers

Whole blood and circulating immuno-inflammatory markers will be measured on hospital arrival and at 12, 24 and 48 hours later

• Total leukocyte count and differential; neutrophil and monocyte surface expression of cellular adhesion molecules and degranulation markers: L-selectin (CD62L) and β_2_-integrin (CD11b) [36]

• Leukocyte apoptotic/necrotic surface and intracellular markers (Annexin V-PE, 7-AAD, Active Caspase-3, Fas (CD95), FasL (CD178) [37-42]

• Soluble pro-/anti-apoptotic molecules (sCD95, sCD95L, TNF-RI, sFas/FasL)[43]

• Leukocyte and endothelial-derived serum soluble adhesion molecule concentrations: intercellular adhesion molecule-1 (sICAM-1), vascular adhesion molecule-1 (sVCAM-1), sE-selectin, sL-selectin [44-46]

• Pro and anti-inflammatory cytokine expression: tumour necrosis factor (TNF)-α, and interleukin (IL)-10 [37,47,48];

• PT/PTT, tissue factor (TF), thrombomodulin (TM), fibrinogen, platelet count and Hg; Ionized calcium, and pH [49]

• Serum sodium, chloride and osmolarity

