### Analysis Plan

This is a feasibility study of two year's duration with a projected screening of 130 patients and recruitment of 100. The primary outcome measure, change in the proportion surviving 30 days post trauma between the treatment and control groups, will be analyzed by means of a generalized linear mixed model which included covariates of interest. The two groups are not expected to be different at baseline, and it is hypothesized that the treatment group would show a 20% decrease in mortality at 30 days post trauma whereas the control group would remain unchanged. To derive a reduced subset of risk factors for the predictor models, acceptable model building strategies are planned (i.e. dropping variables showing extremely small variability and those found to be highly correlated (i.e. correlation coefficient ≥0.8)). Treatment and time factors will be analyzed using a generalized linear mixed models of the secondary outcome repeated measures: the change in mortality after discharge over time as well as the neurocognitive and neuropsychological outcome summary scores. For secondary outcome analyses, the alpha will be adjusted to account for multiple comparisons. Where there is more than one measure for a neuropsychological test (e.g., processing speed, working memory, visuospatial, language, verbal memory, non-verbal memory - with the exception of executive processes, since different measures relate to different brain regions), a composite or prototypical measure will be derived from group comparison. Serial changes in all secondary immune modulation measures, neuro-biomarkers, neurocognitive and neuropsychological outcomes, and structural imaging measures will be evaluated by two-way ANOVA for repeated measures. All analysis will be conducted blinded to treatment assignment.

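### Blood markers are timed from emergency department arrival and analysed at nominal times, so samples, above all the arrival sample, mix different times since injury with no elapsed-time term

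*Protocol article*

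**What the plan says.** Three clocks run in the protocol article. Under Intervention Protocol the infusion is tied to the call: "The study solution is started within 4 hours of the time the emergency call was received at ambulance dispatch". The same section ties blood sampling to hospital arrival: "Samples of peripheral blood will be collected upon emergency department (ED) arrival, 12, 24 and 48 hours after ED arrival". Cellular and Molecular Biomarkers repeats that schedule: "Whole blood and circulating immuno-inflammatory markers will be measured on hospital arrival and at 12, 24 and 48 hours later". Injury has no clock of its own; the emergency call is its nearest proxy.

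Setting pools Toronto land ambulances with a helicopter base "providing responses from accident scenes outside the city of Toronto within south central Ontario".

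For serial changes in immune markers and neuro-biomarkers, Analysis Plan names one method: they "will be evaluated by two-way ANOVA for repeated measures". A secondary objective is "evaluating the role of serum neuro-biomarkers in predicting patient outcome and clinical response to HSD intervention". For prediction the article gives only a general rule, "To derive a reduced subset of risk factors for the predictor models, acceptable model building strategies are planned", and lists no candidate variables.

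**The concern.** A two-way repeated-measures ANOVA on this schedule has arm and nominal time (arrival, 12, 24, 48 hours) as its factors. It cannot use each patient's actual elapsed time. Two patients with the same injury and the same arm may give their arrival samples at quite different times after injury, and the analysis treats them as exchangeable.

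Two uses of the data are exposed. In the randomised comparison, variation in delay adds noise. In the marker-outcome analysis, which is not randomised, delay can do more. If it shifts only the marker, it weakens the association. If it also relates to outcome, for instance through distance or transport mode, it confounds the association. Background places the interest in immunomodulation within the first 24 hours, where a given delay is largest relative to the nominal time.

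**Working it through.** The plan states no figure on this point, so there is none to reproduce. The check asks how much a spread in delay could matter.

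**Inputs from the article.** Samples at 0, 12, 24 and 48 hours after ED arrival; infusion start within 4 hours of the call; 100 patients, taken as 50 per arm (equal allocation is inferred from packages issued in blocks of two).

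**Assumptions, none given in the article.** Spread W of the call-to-arrival delay: 2 or 4 hours, uniform. Exponential decline with half-life h: 2 to 24 hours. Between-patient SD s on the log scale: 0.5 or 1.0. Two-sided alpha 0.05. The 4-hour rule limits call to infusion start, not call to arrival, so W = 4 is a scenario and not a documented spread.

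**1. What a nominal time covers.** For an offset between 0 and W = 4 hours, arrival covers 0–4 hours, the 12-hour sample 12–16 (4/12 = 33%), the 24-hour sample 24–28 (17%) and the 48-hour sample 48–52 (8%). With W = 2 the last three are 17%, 8% and 4%. A minimum delay common to all patients would shift both ends of each range.

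**2. Level difference from timing alone.** Ratio between the earliest and latest patient = 2^(W/h). With W = 4: 4.0 at h = 2, 1.59 at h = 6, 1.26 at h = 12, 1.12 at h = 24.

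**3. Precision of a between-arm contrast.** Variance ratio = 1 + [(ln 2 / h)² × W² / 12] / s². For h = 2, W = 4, s = 0.5: (0.3466)² × 16/12 = 0.160, and 0.160 / 0.25 = 0.64, so the ratio is 1.64. The effect is set to give 80% power at 50 per arm without delay.

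| h (hours) | W (hours) | s | Variance ratio | Power | Correlation factor |
|---|---|---|---|---|---|
| 2 | 4 | 0.5 | 1.64 | 59% | 0.78 |
| 2 | 4 | 1.0 | 1.16 | 74% | 0.93 |
| 2 | 2 | 0.5 | 1.16 | 74% | 0.93 |
| 2 | 2 | 1.0 | 1.04 | 78% | 0.98 |
| 6 | 4 | 0.5 | 1.07 | 77% | 0.97 |
| 24 | 4 | 0.5 | 1.00 | 80% | 1.00 |

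The last column, 1/√(variance ratio), is the factor by which a marker-outcome correlation shrinks if delay is pure noise.

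**4. Which ANOVA tests are affected.** Under exponential decline, log level = aᵢ − k(Dᵢ + t), where Dᵢ is the patient's delay and k = ln 2 / h. The change from arrival to 12 hours is −12k, free of Dᵢ. On the log scale the subject effect absorbs the delay, so the time and treatment-by-time tests lose nothing. The loss in step 3 applies to a contrast at a single visit and to the between-arm main effect.

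**5. Bias of the arm comparison.** A simulation of 20,000 trials with delay independent of arm (h = 2, W = 4, s = 0.5) gave a type I error of 0.051. There is no inflation.

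**The case against.** The strongest reply has five parts.

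- **Prediction.** A reader might infer that the prediction models ignore delay and are therefore biased. The article does not show this. It lists no predictors, and time from call or transport mode may be among the candidates. Such lists are commonly left to the full protocol or analysis plan. This part stands: the point is a risk, not a demonstrated bias. Nor is prediction tied to the arrival sample; later samples exist, where the offset is relatively smaller.
- **Serial change.** The ANOVA is applied to serial changes, and step 4 shows that these are protected when log decline is linear. This stands and narrows the loss to the arrival contrast and the between-arm main effect. It does not cover markers that rise and then fall, or analysis on the raw scale.
- **Extreme inputs.** A reader might take the 4-hour limit as the spread of arrival times and add a 1-hour half-life, for a 2^4 = 16-fold difference. The limit does not bound arrival, and a 1-hour half-life implies a 2^12 = 4096-fold fall by 12 hours, which hardly fits sampling out to 48 hours.
- **Transport mode.** The article gives no transport times and no land/air split, so a systematic difference is an inference. Issuing packages in pairs to each vehicle or aircraft also helps balance the arms within mode. Both are fair, and the second supports the conclusion of no bias between arms; neither helps the marker-outcome analysis.
- **Infusion time.** A reader might want the arm comparison adjusted for time from infusion start as well. Paramedics see the assignment at package opening, so this variable follows allocation. Control saline follows a paramedic protocol while HSD is a single dose, so the variable need not mean the same in both arms. Adjusting for it could bias an unbiased comparison.

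What remains is a named method that cannot use elapsed time, on a sampling scheme in which elapsed time varies. That is a stated choice and not an omission of detail.

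**Conclusion.** The point holds in limited form. Nominal times mix different times since injury, most of all at arrival, and the named ANOVA does not account for it. The HSD versus saline comparison is not biased, provided the assigned fluid does not change how quickly patients reach hospital. The possible loss runs from nearly nothing for slowly changing markers to a fall from 80% to 59% power in the least favourable case tabulated; half-lives, spreads and SDs are all assumed. Marker-outcome analyses are at risk of attenuation (factor 0.78 to about 1.00 in these scenarios) or of confounding, whose direction and size the article does not allow one to state. Feasibility endpoints and 30-day survival are untouched. The change is worth making because it is cheap, but it is not critical to the trial.

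**What to change.** - Replace the two-way ANOVA for serial blood markers with a mixed model containing arm, nominal visit, arm-by-visit, actual time from the emergency call to each sample, and transport mode (land or air), with a patient-level random effect. Analysis Plan already uses generalized linear mixed models for other repeated outcomes, so this adds no new method.
- Include time from call to sample in every model that predicts outcome from the arrival sample.
- Do not adjust the arm comparison for time from infusion start. Report it descriptively by arm, or use it in a labelled sensitivity analysis. Report call-to-arrival time by arm as well, to check that it does not differ.

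The cost is one or two degrees of freedom per model (one for a common time slope, one for mode), with no extra samples or patients. Call and infusion-start times are needed to apply the 4-hour rule, and arrival time is needed to schedule the draws. Actual draw times are presumed to be recorded; the case report forms are not shown, so this should be confirmed.

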### Study outcomes

#### Survival

The primary clinical outcome is survival at 30 days.

Secondary clinical outcomes are survival at 48 hours and to hospital discharge.

#### Neurocognitive Outcomes

At discharge:

• Cerebral Performance Category [14]

At 4 months:

• Functional Independence Measure (FIM)[15]

• Disability Rating Scale (DRS) [16-19]

• Glasgow Outcome Scale (GOS)[16,20,21]

• Glasgow Outcome Scale Extended (GOS Extended)[16,20]

#### Neuropsychological Outcomes

At 4 months:

• Learning and Memory

○California Verbal Learning Test[22]

○Wechsler Memory Scale-Revised Immediate and Delayed Visual Reproduction[23]

○Rey-Osterreith Immediate and Delayed Memory[24]

• Working Memory

○WMS-R Backward Digit Span[23]

• Executive Function

○FAS Verbal Fluency[25]

○Wisconsin Card Sorting Test[26]

○Trail Making Test Parts A & B[27]]

○Stroop Test[28]

○Object Alternation[29]

○WMS-R Forward Digit Span[23]

• Language Function

○Boston Naming Test[27]

○Semantic Fluency[25]

• Visuospatial Function

○Judgment of Line Orientation[30]

○Facial Recognition[30]

• Speed of Processing

○WAIS-R Digit Symbol[31]

○Trail Making Test Part A[27]

• Beck Depression Scale[32].

A focused attention reaction time test[33,34] with varying levels of complexity will be administered at 12 months.

### Structural Outcomes

The structural brain parameters will be evaluated by MRI as described above [7-10] (Additional File 4, 5, 6, 7) and will be measured by a published protocol [8] (Additional File 8, 9). This includes evaluation of:

• Total brain volume and regional volumes (frontal anterior and medial temporal) and medial temporal to be the width [8] (Proton Density T2T1-Weighted) [7]

• Fractional Anistropy (Diffusion Tensor Imaging)

• N-acetyl-aspartate/creatinine ratio (Proton magnetic resonance spectroscopy) [9,10]

• Haemosiderin deposits on gradient echo MRI

• Serum S100B astrocytosis marker of brain injury and C Reactive Protein [35]

### Cellular and Molecular Biomarkers

Whole blood and circulating immuno-inflammatory markers will be measured on hospital arrival and at 12, 24 and 48 hours later

• Total leukocyte count and differential; neutrophil and monocyte surface expression of cellular adhesion molecules and degranulation markers: L-selectin (CD62L) and β_2_-integrin (CD11b) [36]

• Leukocyte apoptotic/necrotic surface and intracellular markers (Annexin V-PE, 7-AAD, Active Caspase-3, Fas (CD95), FasL (CD178) [37-42]

• Soluble pro-/anti-apoptotic molecules (sCD95, sCD95L, TNF-RI, sFas/FasL)[43]

• Leukocyte and endothelial-derived serum soluble adhesion molecule concentrations: intercellular adhesion molecule-1 (sICAM-1), vascular adhesion molecule-1 (sVCAM-1), sE-selectin, sL-selectin [44-46]

• Pro and anti-inflammatory cytokine expression: tumour necrosis factor (TNF)-α, and interleukin (IL)-10 [37,47,48];

• PT/PTT, tissue factor (TF), thrombomodulin (TM), fibrinogen, platelet count and Hg; Ionized calcium, and pH [49]

• Serum sodium, chloride and osmolarity

### Safety and Dependability

The Paramedic Data Checklist (Additional File 10) and both the land and air prehospital (Additional File 11&12) and inhospital (Additional File 13) Case Report Forms explicitly ask whether or not adverse drug reactions with a definite causal relationship to the HSD have occurred. These adverse drug reactions will be predetermined by the Steering Committee based on the literature where possible. (Table 1) The Steering Committee will validate all outcomes and determined adverse events blinded to treatment assignment. This feasibility trial is approved by the Institutional Research Ethics Board.

**Table 1 T1:** Adverse Event Definitions

Event	Expected	Unexpected
**Brain Injury** **(Serious)**	**Demyelination** Any text reference in imaging reports to 'Central Pontine Myelinosis or Pontine Hyperintensity' in any MRI report during hospital stay	**Subarachnoid Hemmorhage** Any text reference in imaging reports of CT of MRI within 24 hours of arrival to Emergency Department to 'Subarachnoid Hemmorhage or SAH' when the first CT scan was normal

**Anaphylactoid Reaction** **(Serious)**	Any text reference in physician notes within the first 24 hours of arrival to Emergency Department to 'anaphylactoid reaction'	

**Prolonged Partial Thromboplastin Time** **(Non serious)**	Normal up to 40 May see up to 85 with HSD	> 100

**International Normalized Ratio** **(Non serious)**	Normal up to 1.5 May see up to 3.0 with HSD	> 3.0

**Serum Sodium** **(Non serious)**	Normal range 135-147 May see up to 158 with HSD	> 160

**Serum Osmolarity** **(Non serious)**	Normal range 310-330 May see up to 350 with HSD without alcohol	> 350 without alcohols

**Serum Chloride** **(Non serious)**	Normal range 96-108 May see up to 145	>150

**Rouleau formation** **(Non serious)**	May be present	

MRI Magnetic Resonance Imaging

CT Computerized Tomography Scan

SAH Subarachnoid Hemmorhage

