## Methods/Design

### Study design

The Toronto Prehospital Hypertonic Resuscitation-Head Injury and Multi Organ Dysfunction Trial (TOPHR HIT) is a randomized, placebo-controlled trial of blunt trauma patients with head injuries. The study compares a group receiving normal saline according to a paramedic's protocol, with a treatment group receiving a single dose 250 ml of 7.5% hypertonic saline in 6% dextran 70 (RescueFlow^® ^BioPhausia AB, Stockholm Sweden). The study was approved by the Canadian Therapeutic Products Directorate Control Number 092523 and registered at http://www.clinical.trials.gov. Inclusion and exclusion criteria are summarized in Additional file 1.

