### Randomization

The study employs a block randomization by station derived from a computer-generated random number table. Blocks of two study packages are assigned to each ambulance vehicle/aircraft. Paramedics are blinded to the treatment assigned until package opening. A field logistics research coordinator is responsible for randomization compliance at the vehicle level through daily checks. Compliance at the patient will be verified through the randomization number of the product label and recorded on the data checklist.

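### Adverse events are to be determined blind, but the HSD-attribution question and four of Table 1's five numeric Expected ranges cannot be applied without knowing the arm

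*Protocol article*

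**What the plan says.** Under Study design, the Protocol article calls the study a "randomized, placebo-controlled trial of blunt trauma patients with head injuries"; the abstract uses the same label. The control is a "group receiving normal saline according to a paramedic's protocol", set against a "treatment group receiving a single dose 250 ml of 7.5% hypertonic saline in 6% dextran 70". Under Randomization: "Paramedics are blinded to the treatment assigned until package opening".

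Under Safety and Dependability, the paramedic checklist and the prehospital and in-hospital case report forms are said to ask about drug reactions that HSD definitely caused. The Steering Committee then "will validate all outcomes and determined adverse events blinded to treatment assignment". Table 1 sorts events into Expected and Unexpected. Its sodium row, for example, gives as Expected: "Normal range 135-147 May see up to 158 with HSD". Data Management says that paramedics complete the checklist. The Analysis Plan adds: "All analysis will be conducted blinded to treatment assignment".

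The Study Objective section lists the adverse event rate with HSD infusion as the fourth of four primary feasibility endpoints.

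**The concern.** A committee that does not know the arm cannot say that a reaction was definitely due to HSD, and cannot use a range that is defined for patients given HSD. If both are needed to determine adverse events, the blinding claim and the definitions cannot both stand as written.

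One of the four primary feasibility endpoints is affected, in a study meant to inform a definitive multicentre trial. Readers would credit the adverse event results with a protection that part of the process lacks. A question that only an HSD patient can answer yes to also gives no saline rate to set beside the HSD rate. The Discussion offers the forms for reuse by other trials, so the wording could spread.

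**Working it through.** No sample size, power or alpha figure bears on this point, so the check sets the statements side by side.

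**Step 1: who knows the arm, and when.**
- Paramedics: blinded until the package is opened, so they know the arm once treatment starts (Randomization). They complete the checklist (Data Management), which carries the HSD-reaction question (Safety and Dependability). Reactions recorded in the field are therefore ascertained by someone who knows the arm.
- In-hospital abstractors: blinding not stated in the article.
- Steering Committee: stated to be blinded.
- Analysis: stated to be blinded.

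**Step 2: the causality question.** To answer yes, the recorder or adjudicator must hold that HSD was given and caused the event. For a saline patient the only correct answer is no. Across both arms, the count from this question is zero in the control group by construction, whatever happened to those patients.

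**Step 3: Table 1, numeric laboratory rows.**

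| Row | Normal limit (upper) | Expected up to | Expected range tied to HSD? | Unexpected | Unexpected tied to arm? |
|---|---|---|---|---|---|
| PTT | 40 | 85 | yes | > 100 | no |
| INR | 1.5 | 3.0 | yes | > 3.0 | no |
| Sodium | 147 | 158 | yes | > 160 | no |
| Osmolarity | 330 | 350 (without alcohol) | yes | > 350 (without alcohols) | no |
| Chloride | 108 | 145 | no | > 150 | no |

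Four of five rows tie the Expected range to HSD; none of five ties the Unexpected cut-off to an arm. For values above the normal limit and up to the HSD limit (PTT 40 to 85, INR 1.5 to 3.0, sodium 147 to 158, osmolarity 330 to 350), the table gives no reading for a saline patient. A sodium of 155 fits the Expected wording if the patient had HSD. If the patient had saline, it is above normal, below the Unexpected cut-off, and has no category. Placing it needs the arm.

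**Step 4: the other rows.** Demyelination, subarachnoid haemorrhage and anaphylactoid reaction are defined by text in imaging reports or physician notes. The rouleaux row does not mention HSD. All can be applied without the arm.

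**Step 5: the endpoint.** If endpoint 4 covers both arms, the HSD-worded question supplies no usable control rate (step 2). If it covers HSD recipients only, it has no comparator, and the attribution still presupposes the arm.

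**The case against.** The strongest reply is that an open field phase with blinded adjudication is a coherent design. The article limits the paramedics' blinding openly, claims blinding only for the committee and the analysis, and nowhere claims lasting blinding in the field. That stands. A reader might infer that the Randomization section by itself contradicts the committee's blinding; it does not. The conflict is with the attribution question and the Expected column.

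Second, most Table 1 events come from hospital records, and the article does not say whether in-hospital staff know the arm. That also stands. A reader might infer that the whole adverse event endpoint is recorded and classified open-label. The documents support this only for reactions recorded by paramedics, for attribution to HSD, and for the Expected category in four rows.

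Third, the endpoint may be meant as a rate among HSD recipients, so that a control rate was never intended. This is a fair reading, but it does not let a blinded committee attribute an event to HSD. It also leaves the HSD rate with nothing to set it against, although a randomised control group is at hand.

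Fourth, the HSD notes could be meant as one Expected range for every patient. That would remove the difficulty in Table 1, but the table does not say so.

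A reader might also infer that the committee could identify the arm from sodium at some calculable rate. The article gives no mean change and no standard deviation. The distance from 147 to 158 is a gap between two upper limits, not a mean shift. It is fair to say that the table expects HSD to move these values; no guessing rate follows from that.

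**Conclusion.** The point holds in a limited form. As written, attribution of reactions to HSD and the Expected category for PTT, INR, sodium and osmolarity (four of five numeric laboratory rows) cannot be applied blind, and field reactions are ascertained with the arm known. The HSD-worded question gives no control rate for one of the four primary feasibility endpoints.

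The five Unexpected cut-offs, the chloride row and the text-based serious events are arm-neutral, and survival at 30 days is little exposed to assessor bias. The calculation is a count of rows and needs no assumed figure. The conclusion does rest on the article's description of the forms, since the forms themselves are in additional files that are not shown, and on reading the HSD notes in Table 1 as applying to HSD patients.

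The placebo-controlled label is loose rather than contradictory: no masked infusion is described and the arm is seen at package opening.

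**What to change.** 1. Ask, in both arms and in the same words, about any reaction after the study fluid. Leave attribution to HSD out of the form.
2. Classify laboratory values by program against one set of limits applied identically to both arms, and report the counts by arm. The Unexpected cut-offs already work this way. Which limits to use is for the sponsor to decide.
3. Have the committee adjudicate the clinical events from files without the laboratory values that Table 1 expects HSD to change.
4. Describe the trial as saline-controlled, open in the field after package opening, with blinded adjudication of clinical events, and state who is blinded at each step.

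The cost is wording, some file preparation and a less favourable description of the blinding. No additional measurements or visits are needed. Laboratory data need not be held back until other analyses are locked; that would delay safety data, and this remedy does not depend on it.

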### Data Management

Paramedics complete a data checklist (Additional File 10) and standardized provincial patient care record. A single paramedic data abstractor will abstract data from the paramedic checklist and patient care record onto a prehospital case report form (Additional File 11). Site specific inhospital research staff will abstract data from the patient's chart daily and completed an inhospital case report form (Additional File 13). In-hospital patient data includes the interpretation of head CT scans employing the Marshall Classification system [50] as well as the Injury Severity Score [51]. Measures of organ dysfunction: Acute Physiologic and Chronic Health Evaluation (APACHE II)[52,53], Sequential Organ Failure Assessment (SOFA) [54] and Multiple Organ Dysfunction Score (MODS)[55] will be evaluated at ICU admission. In addition, SOFA and MODS will be recorded every other day until ICU discharge. Data entry onto a web based (prehospital data) or SAS version 8.0 interface (inhospital and follow up data) will be performed by a single trained data entry specialist.

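### Table 1 defines the three serious adverse events by mention of fixed phrases, so true events in other words can be missed and non-affirmed mentions are not excluded

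*Protocol article*

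**What the plan says.** Table 1 (Safety and Dependability) marks three events as serious, each defined by a mention in the record:

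- **Subarachnoid haemorrhage** (unexpected column): "Any text reference in imaging reports of CT of MRI within 24 hours of arrival to Emergency Department to 'Subarachnoid Hemmorhage or SAH", with the condition "when the first CT scan was normal".
- **Demyelination** (expected column): "Any text reference in imaging reports to 'Central Pontine Myelinosis or Pontine Hyperintensity' in any MRI report during hospital stay".
- **Anaphylactoid reaction** (expected column): "Any text reference in physician notes within the first 24 hours of arrival to Emergency Department to 'anaphylactoid reaction".

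The same section says that the paramedic checklist and the case report forms "explicitly ask whether or not adverse drug reactions with a definite causal relationship to the HSD have occurred". The Steering Committee fixes these reactions in advance, and the text refers to Table 1 for them. It adds: "The Steering Committee will validate all outcomes and determined adverse events blinded to treatment assignment".

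Data Management describes how the in-hospital record is read: "Site specific inhospital research staff will abstract data from the patient's chart daily".

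Study Objective lists the rate of adverse events with the HSD infusion as the fourth primary feasibility objective.

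**The concern.** A case definition should separate patients who had the event from those who did not. These three definitions ask only whether certain words appear. They do not ask whether the finding was affirmed, and they do not accept the same condition under another name. Such a rule can err in both directions.

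The missed events matter more. If a report is never flagged, a later check of flagged events has nothing to work on. Over-inclusion is easier to put right, because someone downstream can read the report and reject it.

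At stake is a primary feasibility result that may inform the definitive multicentre trial. Serious events are likely to be few among the 100 patients to be recruited (Analysis Plan). If the arms are about equal (an assumption; the article states no arm sizes), one misclassified event moves an arm's rate by 1/50 = 2 percentage points. That figure shows only how sensitive the rate is. It does not say how many events would be misclassified.

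**Working it through.** The article states no figure on this point, so there is nothing to reproduce. The check has two steps: apply the written definitions to typical report wordings, then ask whether any later step described in the article corrects the result.

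**Step 1. The definitions applied literally**

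| Record | Criterion met? | Correct? |
|---|---|---|
| First CT normal; later report within 24 h affirms SAH | Yes | Yes |
| First CT normal; later report within 24 h says no SAH | Yes, negation is not excluded | No |
| First CT normal; later report within 24 h cannot exclude SAH | Yes | Not an affirmed event |
| First CT not normal; a report says no SAH | No, the first-CT condition fails | Yes |
| First CT normal; the bleed is affirmed within 24 h using neither listed term | No | No, missed |
| In-hospital MRI report affirms 'demyelination' only | No, neither listed phrase appears | No, missed |
| In-hospital MRI report says no pontine hyperintensity | Yes | No |
| Physician note within 24 h says no anaphylactoid reaction | Yes | No |
| Physician note within 24 h describes the same reaction in other words | No | No, missed |

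The demyelination miss needs no outside vocabulary. The word that fails to match is Table 1's own label for the event.

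**Step 2. Later steps that could correct the result**

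| Step in the article | Removes a non-affirmed mention? | Recovers a missed event? |
|---|---|---|
| Chart abstraction by research staff at each site | Possibly, by common sense; no written rule, so sites may differ | Only if staff go beyond the written definition |
| Form question on reactions definitely caused by HSD | Probably; a negated mention cannot be a definite reaction | Not shown; it points back to the Table 1 list and adds a causality requirement |
| Blinded Steering Committee validation | Possibly; the article gives no validation criterion other than Table 1 | Not shown; no review of unflagged reports is described |

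The sentence on the committee may mean that it validates adverse events already determined, or that it also determines them. On either reading, the article does not say that unflagged reports reach it.

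**Result.** Each of the three steps has a plausible way to remove a non-affirmed mention. None is shown to recover an event described in other words.

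**The case against.** The best defence is that the phrases are a sensitive trigger and the committee is the adjudicator, which is an ordinary design. Table 1 heads the imaging cells with the names of the conditions, so the phrases can be read as the way those conditions are picked up from the chart. Research staff read the charts, and no automated search is described. The subarachnoid row is confined to patients with a normal first CT. The form question requires definite causality. A committee that could not reject a plain negation would be validating nothing.

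Most of this stands on the over-inclusion side. A reader might infer that a report stating there is no subarachnoid haemorrhage would be counted as a serious event. The article does not support that, because the first-CT condition, the human abstraction and the blinded validation all stand between the mention and the final count. What remains is that no written criterion tells the committee to discard such mentions, and Table 1 taken at its word says that any mention suffices.

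The defence is weaker on missed events. A trigger limited to fixed phrases is not sensitive to other wording, and adjudication of what was flagged does not make it so. It is fair to say that one of the demyelination phrases is a descriptive imaging term, so that row is not tied to a single diagnostic label. The in-hospital case report form is cited as an additional file but not shown, and it may carry fuller instructions. If so, it would differ from the published definition, and the two should be aligned.

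**Conclusion.** The concern holds in a limited form. Table 1 states a rule that misclassifies when followed literally, for events that feed a primary feasibility objective. The missed-event side is the firmer part: no described step is shown to recover a differently worded event. The over-inclusion side is a gap in the written criterion, which the blinded committee may well close in practice.

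The size cannot be estimated. The article does not say how many patients would have a normal first CT, how many would be imaged again within 24 hours, or how often reports name a finding in order to exclude it or describe it in other words. A reader might go further and infer that most counted serious events would be false, or that the rate would reflect reporting style instead of harm. The documents support neither inference, because both need frequencies that are not given and both assume that validation removes nothing.

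The conclusion rests on the published wording of Table 1 and on the abstraction and validation steps as the article describes them. Forms that are not shown could reduce the problem.

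**What to change.** Reword the three serious-event cells in Table 1 and the matching abstraction instruction:

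1. In the two imaging cells, replace 'any text reference' with a report that affirms the condition as a new finding. In the anaphylactoid cell, require a physician record that affirms the reaction. Keep the existing time windows and the first-CT condition.
2. State that negated, 'cannot exclude' and historical mentions do not count.
3. Accept equivalent terms for the same condition, so that the listed phrases become examples and not the whole definition.
4. State that abstractors forward any report that may qualify, and that the Steering Committee, blinded to assignment, validates against this rule.

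The change needs no new data, patients or staff. The small downside is that a few more ambiguous reports go to the committee, which already validates events.
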